#### App Satisfaction Survey

In the week 6 survey, participants will receive the ReNeuWell App Satisfaction Survey, containing a range of questions regarding the participant’s opinion of the app and what they liked or disliked about it. This questionnaire is provided in the supplementary materials.

#### Adverse Event Assessment

Each survey will conclude with an Adverse Event Assessment, constituting a text box in which the participant can report any aspect of the app or survey that caused discomfort or distress. If the participant has no adverse events to report, they will leave the box empty and finish the survey. This section of the survey also provides the following reminder: “In the App Settings menu, we have provided contact details for Mental Health Support Services for your country, should you ever feel distressed and require additional mental health support.” The Adverse Event Assessment is provided in the supplementary Materials.

#### App usage metrics

Data regarding participant usage metrics (eg, which activities they completed, how much time they spent using the app) will be recorded within the app and via Google back-end software (Firebase).

#### Anonymity and confidentiality

All data collected by ReNeuWell will be automatically uploaded to a secure, dedicated server (located in Australia). On this server, users’ account data (ie, names and email addresses) are stored separately from their survey data and are only accessible using a permissions-based system. This ensures security of the data over and above encryption. The survey data will not include any personally identifying information but rather a trial participant ID number that is not shared with the user. Only the research team and app development team (Miroma Project Factory) will have access to the server. The de-identified data will then be downloaded directly from this server onto the secure internal server at Neuroscience Research Australia (NeuRA) for storage and analysis. Only the research team will have access to the data.

#### Data availability

Per ethical requirements and participant consent, data will not be shared beyond the research team.

#### Statistical analysis

The primary outcomes for this RCT will be the participants’ levels of both mental well-being (as measured by the COMPAS-W) and psychological distress (as measured by the DASS-21). The secondary outcomes will be psychological distress as measured by the K10 and work performance. Potential moderator variables include levels of usage and enjoyment of the app, past mental illness, lifestyle habits, baseline mental health levels and demographic characteristics such as age, sex, education, or occupation.

The initial analyses will be conducted on an intention-to-treat basis and followed by per-protocol analyses. Missing values will be estimated via multiple imputation. The hypotheses will be tested via a linear mixed model estimating the group-by-time interaction effects on the outcome variables. It is hypothesised that levels of mental well-being (COMPAS-W) will increase and levels of psychological distress (DASS-21) will decrease in the training condition relative to the control condition. We will also test for group-by-time interaction effects on work performance and the K10 measure of psychological distress. Any interaction effect may itself be moderated by variables such as age, sex, education, occupation, psychiatric history, lifestyle habits, app usage metrics or baseline mental health levels. Furthermore, we will assess user engagement and retention by computing statistics on the number of participants, the levels of app usage and the levels of attrition relative to the overall number of app downloads. We will also use week 1 and 6 survey responses to examine possible differences between participants who withdraw after these timepoints and those who remain in the study until the week 12 survey, allowing us to interpret our findings with respect to any such differences.

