#### Sample size

The minimum sample size was calculated with the software package G*Power (V.3.1.9.2).^50 51^ The type 1 error rate was set at the conventional level of 0.05. With the desired power of 95% and assuming a correlation of 0.5 between the repeated outcome measures, our calculations determined that a total sample size of 324 participants would be needed to detect a small group-by-time interaction effect (partial η^2^=0.01) with two conditions and two measurement occasions (our study has three measurement occasions, but the second occasion is the primary endpoint of the study, and a power calculation with two occasions is stricter than one with three). However, given that app-based interventions demand relatively low commitment from participants, it is reasonable to assume an attrition rate of at least 50% by the second measurement occasion. Indeed, a recent meta-analysis of RCTs of smartphone interventions^52^ found attrition rates of 53.4% between weeks 9 and 12. Therefore, we set our target sample size at 486 participants, with 243 in each condition.

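### With at least half of week 6 outcomes expected to be missing, mostly among people who stopped using the app, missing-at-random imputation could overstate the intention-to-treat effect by a factor of 1.0 to about 2

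*Protocol article*

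**What the plan says.** All references are to the protocol article.

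- **Statistical analysis.** "The initial analyses will be conducted on an intention-to-treat basis and followed by per-protocol analyses". For missing outcomes: "Missing values will be estimated via multiple imputation". For the test: "The hypotheses will be tested via a linear mixed model estimating the group-by-time interaction effects on the outcome variables". The section also plans to "examine possible differences between participants who withdraw after these timepoints and those who remain in the study until the week 12 survey", as an aid to interpretation.
- **Sample size.** The authors consider that "it is reasonable to assume an attrition rate of at least 50% by the second measurement occasion", and cite a meta-analysis that "found attrition rates of 53.4% between weeks 9 and 12". Week 6 is the second occasion and the primary endpoint (Instructions and timeline).
- **Survey measures.** Each survey is given when the participant first opens the app in the relevant week. Recruitment adds that everything is delivered through the app, and no other route for collecting outcomes is described.
- **The ReNeuWell app.** A participant who withdraws may carry on as a paying user.
- **App usage metrics.** "Data regarding participant usage metrics (eg, which activities they completed, how much time they spent using the app) will be recorded". The Statistical analysis section uses these data as possible moderators and for engagement statistics.

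**The concern.** An intention-to-treat effect is the effect of being given the training version, including for people who soon stop using it. Here, stopping use and having no outcome are linked by design: someone who no longer opens the app cannot answer the week 6 survey. On the article's own expectation, at least half of the primary-endpoint values will be filled in by a model.

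Imputation under missing at random, with arm in the model, predicts a training-arm leaver's week 6 score from training-arm responders with similar recorded data. If leavers kept less of the benefit than responders, and nothing in the model captures this, the result is not the intention-to-treat effect. It moves towards the effect that would be seen if leavers had done as well as responders. At this level of missingness, the size of the primary result, and possibly its significance, would depend on that assumption about as much as on the data.

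**Working it through.** **1. The plan's own figure.** Inputs from the Sample size section: partial η² = 0.01, correlation ρ = 0.5, two groups, m = 2 occasions, α = 0.05, power 95%.

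- f² = 0.01/0.99 = 0.0101.
- Noncentrality λ = N·m·f²/(1−ρ). At N = 324, λ = 324 × 2 × 0.0101/0.5 ≈ 13.1, with 1 and 322 degrees of freedom.
- Power is 0.950, and 324 is the smallest N that reaches 95%. The stated figure reproduces.
- In SD units, the variance of change is 2(1−ρ) = 1, so λ = (N/4)·δ². Then δ² = 4 × 2 × 0.0101/0.5 = 0.162 and δ ≈ 0.40 SD.

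**2. Overstatement factor.** Let d be the share missing, equal in both arms. Let δ be the effect among responders, and r the share of that effect kept by those with missing outcomes.

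- True intention-to-treat effect: δ·[(1−d) + d·r].
- Missing-at-random estimate with arm in the model and no variable that separates leavers from responders: δ.
- Ratio: 1/[(1−d) + d·r].

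The value d = 0.50 is the article's lower bound for week 6. The value 0.534 is its cited meta-analytic rate, which refers to weeks 9 to 12 and serves here as a second value. The value of r is an assumption, shown over its range.

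| r | d = 0.50 | d = 0.534 |
|---|---|---|
| 1 | 1.00 | 1.00 |
| 0.75 | 1.14 | 1.15 |
| 0.5 | 1.33 | 1.36 |
| 0.25 | 1.60 | 1.67 |
| 0 | 2.00 | 2.15 |

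For example, 1/(0.5 + 0.5 × 0.5) = 1/0.75 = 1.33, and 1/(0.466 + 0) = 2.15.

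At the design effect with d = 0.50, about 0.40 SD would be reported. The true effect would be 0.40 × 0.5 = 0.20 SD at r = 0, or 0.40 × 0.75 = 0.30 SD at r = 0.5.

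**3. Simulation check.** 243 per arm, ρ = 0.5, 1,500 runs, imputing week 6 from baseline and arm.

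- r = 0: ratios 1.98 and 2.16 (d = 0.50 and 0.534).
- r = 0.5: ratios 1.32 and 1.36.
- r = 1: ratios 0.99 and 1.01.

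With arm left out of the imputation model, the ratios were about 1.0 at r = 0, 0.64 to 0.66 at r = 0.5 and 0.46 to 0.49 at r = 1. That choice understates the effect whenever leavers keep some benefit.

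**4. Do the other stated provisions cover it?**

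- The linear mixed model also relies on missing at random, so agreement between it and the imputed analysis would not be independent support.
- The comparison of withdrawers with stayers is descriptive. Anyone lost before week 6 has only week 1 responses, so it cannot show how leavers stood at the primary endpoint.

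**The case against.** The strongest reply is that an article may leave the imputation model, the auxiliary variables and the sensitivity analyses to an analysis plan that is not shown. That is right, and their absence alone is not the point. The point rests on what the article does fix: an intention-to-treat label, multiple imputation, at least 50% attrition at the primary endpoint, and outcome collection that depends on opening the app. Nothing in the article rules out by-arm imputation with usage data, so the fix is compatible with the plan as written.

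Three stronger readings are tempting, and the documents support none of them.

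- *The plan will double the effect.* A factor of 2 at 50% missing needs every leaver to keep none of the benefit and arm to be in the imputation model. The article gives neither. If half the benefit is kept, the factor is 1.33 to 1.36.
- *The false-positive rate will be well above 5%.* With no true effect, that needs dropout to depend on the outcome differently in the two arms. If the dependence is the same in both arms, the rate stays at about 5%. The article gives no ground for such a difference, since both arms receive the same instruction on daily use, the same surveys and the same unlocking rule.
- *A missing survey means non-use, and an answered one means full use.* Withdrawers may continue as paying users. A participant need only open the app once in a week to unlock the next, so some people who do very little will still answer. Responders are therefore a mixture, and r must be read relative to their average benefit.

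It is also fair that control-based imputation is one of several defensible sensitivity analyses. What matters is that one departure from missing at random is named before the data are seen.

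**Conclusion.** The concern holds in a conditional form. With d of 50% to 53.4%, equal in both arms, and missing-at-random imputation that includes arm, the intention-to-treat effect could be overstated by a factor between 1.0 and about 2 (2.15 at the upper value of d). Where it falls depends on how much benefit leavers keep, which the documents do not give and the trial will not observe directly. Attrition above 53.4% would raise the upper end. If usage data already enter the imputation, or if arm is left out, these figures do not apply as they stand. Neither the mixed model nor the withdrawer comparison removes the dependence on this assumption. Multiple imputation is not an error here, but on its own it does not show whether a positive primary result would survive a less favourable view of the leavers.

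**What to change.** Two additions to the Statistical analysis section:

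1. Impute separately by arm, with usage logged before dropout as auxiliary variables (time in the app, activities completed, last active week). This helps only if some low users answer the week 6 survey, so that the relation between usage and outcome can be estimated. In a simulation where they did, the estimate moved from 0.35–0.42 SD to about the true 0.30 SD.
2. For COMPAS-W and DASS-21 at week 6, name one sensitivity analysis. One option is control-based imputation, in which missing training-arm values follow the control arm given baseline. The other is a delta shift in the unfavourable direction, taken to the tipping point. State that any positive result will be reported together with whether it survives this analysis.

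With a responder effect of 0.40 SD and d = 0.50, the control-based estimate would be about 0.40 × 0.5 = 0.20 SD, which matches the r = 0 case.

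The cost is a few lines of code and a short addition to the text. Every variable is already recorded. The drawbacks are somewhat wider intervals and a less favourable sensitivity estimate.

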#### Ethics and dissemination

This protocol has been approved by the Human Research Ethics Committee of the University of New South Wales (reference number: HC210302) and preregistered with the Australian New Zealand Clinical Trials Registry (registration approved on 4 August 2021; trial ID number: ACTRN12621001014842p). Our findings will be published in accordance with this protocol, both in the peer-reviewed literature and on the registry website.

#### Public involvement

Because ReNeuWell is designed for use by the general adult population, it was appropriate to conduct several rounds of consultations with members of the general public throughout the app’s development. During initial design stages, we conducted user acceptance testing with volunteers from the general public, who provided feedback on the app’s design, colours, contents and features. The app was subsequently refined over numerous iterations, after which beta testing was conducted with local community members for feedback on usability and acceptability of the app, including identification of any bugs or feature issues. The app was then refined further and retested in-house across multiple iterations, before being ‘soft launched’ on the Apple Store for additional testing by a new group of local community members (ie, volunteers could download ReNeuWell from the Apple Store for testing purposes).

## Discussion

The field of app-based interventions to improve mental well-being has yielded promising findings to date, but there remains a *research-to-retail gap*,^13 14^ where many studies pertain to apps that are not publicly available, have not been tested in the general population and/or contain proprietary well-being measures that have not been validated in the peer-reviewed literature. Furthermore, few previous studies have been conducted in an ecologically valid setting, where a user freely chooses to download a publicly available app from a mainstream app store and then uses the app as a standalone program without ever needing to interact with another person or entity. On the market side of the gap, many popular apps have remained available on mainstream app stores for years without ever being submitted to peer-reviewed empirical assessment, and some of these apps have product descriptions that make claims of efficacy despite the lack of empirical evidence.^10 12 15 33^

Alongside the research-to-retail gap, another limitation is that most well-being apps cover only one or a few techniques.^32 33^ The literature suggests that mindfulness exercises, which are among the techniques most commonly offered by well-being apps,^14 15^ can indeed be effective for increasing well-being,^7^ but multicomponent interventions (comprising a range of positive psychology exercises) also have efficacy^7^ but have not been offered by many apps previously.^32^ Furthermore, although some well-being apps offer evidence-based exercises,^32^ few if any are informed by a comprehensive, empirically validated model of well-being. The COMPAS-W framework^5^ provides not only a multidimensional description of total well-being, but also a validated scale to measure each dimension and overall well-being.

ReNeuWell is a newly developed iPhone app, grounded in the COMPAS-W model of mental well-being,^5^ which addresses these openings in the literature and in the marketplace, and its evaluation in our upcoming RCT will hopefully address some of the key gaps in our knowledge of mental well-being apps and their effectiveness. ReNeuWell provides a tailored program of daily activities and other resources designed to increase well-being in one or more of the six COMPAS-W dimensions. We aim to determine whether this publicly available, standalone app can promote greater well-being and reduce distress in the general adult population of Apple Store customers who choose to use it.
